### Statement of ethics approval and consent to participate

The study will be executed in accordance with the US National Institute of Health guidelines for research involving human subjects as participants and all methods will be performed in accordance with comparable ethical standards as laid down in the Declaration of Helsinki^33^ and its later amendments. Ethical clearance was obtained from Mbarara University of Science and Technology in Uganda (Ref: MUREC 1/7; 05/5-19) and final ethical approval was granted from the Uganda National Council for Science and Technology, the authority which regulates research in Uganda (Ref. No. SS 5082). It will be prerequisite for each eligible participant to endorse a predesigned informed consent form with their signatures in the presence of principal investigator or designated trainers prior to participation in the study. The official consent form for Mbarara University of Science and Technology will be adopted for this purpose. Participation will be free and voluntary, and participants will have the right to withdraw from the study at their wish. Video recordings will be destroyed 4 months after expert feedback on team performance and retrieval of main content themes for each cycle of training.

### Participant recruitment workflow

The potentially eligible participants will be registered, briefed, and educated about the study 2 weeks prior to the training; and availed links to the educational materials. Consented participants will be recruited for this 2-day event. On the agreed first day of the training, interns and medical trainees will complete pretraining MCQs during the first 40 min in ‘an exam-like’ supervise environment, followed by assignment into random groups. The training will be divided into four modules, that is, (i) introduction to rural trauma systems, primary and secondary survey, (ii) case scenarios, (iii) trauma communication, and (iv) patient safety and process improvement. Each module will be allocated 2 h to make a total of 8 h of ‘continuing medical education’, which is the maximum allowable by the committee on trauma of American College of Surgeons. The first half of the course modules will be delivered during Day 1 and the remaining half on Day 2 of the training. The training for all teams will take place between 9:00 am and 15:00 pm and the venue will be the designated spacious multimedia surgical simulation room located at each of the training hospitals. There will be coffee breaks of 45 min between each 2 h session on each day of the training. The PI will cater for the coffee budget to enhance attendance and time efficiency. The participants will maintain their teams throughout training days. Study participants will be given overall team performance feedback after the last module and each study subject will be asked to complete a 15 min course evaluation form regarding acceptability and relevance of the training at the end of Day 2. Subsequently, trainee participants will be followed up after 3 months (90 days) from Day 1 of the training to complete a 40 min post-training trauma based MCQs in ‘an exam-like’ supervised environment as shown in Figure 1.

**Figure 1 F1:**
[figure not shown]
Flow diagram showing recruitment process of study participants.

## Discussion

Compelling evidence from high-income countries suggest that rural trauma team development course training could improve the efficiency of care and clinical outcomes of patients who sustain trauma^23,34^. In their results, scientists demonstrated that these benefits of rural trauma team training could arise through improved clinicians’ knowledge, and team organization in terms of: leadership, communication, and quick decision-making; subsequently shortening the time to execute treatment or transfer the injured patient to higher level trauma centers^21,22,35^. However, what is defined as ‘rural’ in USA settings is rather not depictive of LMICs. For instance, whereas the decisions for prehospital care and emergency evacuation of injured patients are made by emergency physicians and paramedics, using air-ambulances in high-income countries^34^, these tasks are often executed by allied health, medical trainees, and traffic law enforcement professionals often using public transport in Uganda^36,37^. This timely study will examine the conceptualization of rural trauma team development through providing training capacity to traffic law enforcement and trainee medical professionals who are viewed as potential sustainable human resource for injury care in low-resource settings. Our findings on acceptability and applicability of the proposed training could potentially inform the design of future rural trauma teams in real-world clinical settings of LMICs. Furthermore, when our study findings become available, the results could guide the design of traffic law enforcement and medical curricula in Uganda and similar low resourced settings.

### Study strengths and limitations

There will be some limitations in this study. First, our trauma team simulation with traffic police and students in medical training could arguably differ from the physician-led emergency medical teams in affluent Western countries, consequently limiting the generalizability of our results to LMICs. Secondly, regarding training for police, we hope to emphasize the key communication aspects of evacuation and prehospital safe transportation of injured patients to hospitals. As such, we shall not assess the trauma knowledge based MCQ for law enforcement participants on assumption that they have no pre-existing clinical exposure but information on their trauma nontechnical skills and applicability of the gained knowledge to their work environment will be obtained. Furthermore, medical trainee participants’ knowledge could change with time irrespective of the intervention but we hope that having multiple interrupted time series of intervention sessions at multiple study sites and using time series autoregression models will overcome this obstacle in addition to limiting confounding due to between group differences^38^. Lastly, the mean difference in prepost training MCQs for medical trainees might only depict knowledge improvement which does not necessarily transform to clinical skills that impact patient outcomes. However, the authors plan to transfer this classroom knowledge into clinical practice in a cluster randomized controlled trial to determine whether the apparent knowledge changes during the training are not due to other interventions, impact on clinical time efficiency, and patient outcomes in our constrained resource context.

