### Training procedure, team construct, and course implementation

On average 12 (6–24) training sessions will be conducted per site between 28th of September 2019 and 28th of November 2023. Cohorts of participants will be enrolled every after 3 months to strike a balance between the average duration of surgical internship deployment by the Ugandan ministry of health which lasts 1–5 months, and the surgery clinical rotations for medical students which lasts 2 months. Furthermore, the effects of the training are presumed to ‘decay’ after this period and the authors project to realize the targeted sample size based on the 3 months interval. However, permission will be sought from the ethical committee to extend the study in case the target sample is not obtained during the approved duration of the study. The mode of delivery and content of the RTTDC training will not be modified. The training will be advertised by hospital administrators and class representatives and eligible participants will be recruited based on first come first serve. The training dates will be selected to suit the designated days for clinical grand rounds and/ or continuous professional development sessions so as not to interfere with the university and hospital daily schedules. The investigators will use student unique numbers from university hospital administrators’ database to randomly assign recruited participants into teams and to ensure that each participant is recruited once. The participating law enforcement professionals who will show up for the training will pick ballot papers randomly to be assigned to the already created medical trainee teams. The chief trainer will be a chief surgeon (HL) who attended the RTTDC instructor course. The surgeon will coach two co-trainers who are master of surgery residents undertaking a traumatology rotation, at the participating hospitals to make a total of three trainers. Since the program is aimed at capacity building, and residents directly supervise interns in Uganda, the research and ethics board approved training of residents as opposed to consultants not to over strain the skeleton specialized staff at the study sites. Interns and residents contribute to 75% of the health workforce in public hospitals in Uganda^8^. The program will be designed for two days, targeting 30 participants with a trainer: trainee ratio of 1:10, which is the maximum permissible for each training session according to the committee on trauma of the American college of Surgeons. For each team task, participants will be grouped into teams of five to role play a surgeon, surgeon assistant/intern, an anesthesiologist/anesthetic assistant, an allied health professional (emergency room nurse/laboratory/imaging personnel), and a rescue police (representing paramedics in Uganda’s settings).

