
### Course outcomes

At the end of the training, participants are anticipated to be able to describe components of their current local trauma system (trauma capacity), describe barriers to effective trauma care in their settings, suggest areas for performance improvement, demonstrate concepts of primary survey and secondary survey, know when to make a timely decision to consult or transfer (referral) for definitive care, and understand the link between lower hospital facilities and regional trauma centers. These goals have been set apriority in accordance with the committee on trauma^27^. The participants will complete a paper based pretraining trauma related MCQs before and at 3 months after the training. The method of data collection will remain the same with a target data completion rate of 100% for every series. The prepost training MCQs will be marked by two independent consultant surgeons who are not part of the research team. The marking team will be blinded by what is pretraining or post-training. Since the answers and marking guide are standardized, we anticipate an inter-rater agreement of 100%.

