### Study population

We shall target nursing students and medical students/interns who are often the first contacts to trauma patients in hospital settings and road traffic law enforcement professionals who are often involved in transportation of such patients to hospitals. The accessible population will be those medical trainees/interns completing the surgery rotation during the study period and police officials assigned to complete the training by virtue of their roles.

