### Inclusion criteria

We shall include participants who meet the following criteria: road-traffic police officer, medical intern doctor/nurse, medical student enrolled in Bachelor of medicine and Bachelor of Surgery in clinical years (3rd or 5th) who completed or currently is completing the surgical/traumatology clinical rotation, allied health professional trainee enrolled in Bachelor of Nursing Sciences or Bachelor of Clinical Medicine degree program and is involved in the care of the injured patients or attached to the accident and emergency department during the study period.

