### Statistical analysis

The data will be exported from REDCap to Stata version 15.0 for analysis (StataCorp. 2017. Stata Statistical Software: Release 15. College Station, TX: StataCorp LLC).

We shall test the data for normalcy using the Shapiro–Francia test and normal histogram curves at 95% CI, regarding *P*<0.05 as statistically significant.

If the data are normally distributed, the difference in pretraining and post-training mean scores will be compared using one way analysis of variance (ANOVA) test otherwise nonparametric Friedman test will be used to compare the scores as a measure of knowledge retention, assuming a null hypothesis of no difference. Box plots will be used for data presentation to offer a succinct visual summary of data distribution.

Furthermore, we shall perform Wilcoxon signed rank nonparametric test to examine the difference in the effect the training has on MCQ scores of the various cadres of participants aggregated (3rd year, 5th year, and interns). The median scores for various groups and their corresponding interquartile range will be reported.

The statistical difference in rank sums regarding desirability and relevance of various course themes will be compared between participating cadres using a nonparametric Kruskal–Wallis (H) test.

Lastly, time series regression (ARIMA) models will be used to test for autocorrelation trends in MCQ performance over the study period for the various medical trainee groups.

All the analyses will be performed using Stata 15.0. (StataCorp. 2017. *Stata Statistical Software: Release 15.* College Station, TX: StataCorp LLC); at 95% CI, regarding a 2-tailed *P*-value <0.05 as statistically significant.

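### The interrupted time series and autoregression models cannot do what the limitations section hopes: with one pre and one 90-day post score per trainee, the score gain cannot be attributed to the course

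*Protocol article*

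**What the plan says.** The title, abstract and Study design section call the study an interrupted time series. The measurement schedule is simpler than that. Under Course outcomes, "The participants will complete a paper based pretraining trauma related MCQs before and at 3 months after the training". Participant recruitment workflow fixes the second test: "trainee participants will be followed up after 3 months (90 days) from Day 1 of the training". Training procedure states that "Cohorts of participants will be enrolled every after 3 months" and that student numbers will be used "to ensure that each participant is recruited once".

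Trainees are in clinical training throughout. Study population names "those medical trainees/interns completing the surgery rotation during the study period", and Inclusion criteria admits medical students "who completed or currently is completing the surgical/traumatology clinical rotation".

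In Statistical analysis, pre and post scores are compared by one-way ANOVA, or by the Friedman test if not normal. Separately, "time series regression (ARIMA) models will be used to test for autocorrelation trends in MCQ performance over the study period", by trainee group.

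Study strengths and limitations acknowledges that knowledge could change over time whatever the course does. The authors then hope that "multiple interrupted time series of intervention sessions at multiple study sites and using time series autoregression models will overcome this obstacle". The same section leaves to a later cluster randomized trial the question of whether the knowledge changes are due to something else.

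**The concern.** An interrupted time series separates an intervention from an underlying trend because the same unit is measured several times before the interruption, so the trend can be estimated and projected. Here no trainee has a baseline run. The first participant was recruited on the day the training period opens, and all cohorts are trained. This is a before-after comparison repeated in successive cohorts.

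The first specific objective is the pre/post score comparison, and the Discussion says the results could guide curricula. If the stated remedy is taken at face value, ordinary learning on clinical rotation, or familiarity with the test, would be read as a course effect on the understanding that this bias had been dealt with.

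**Working it through.** **1. Inputs from the protocol article.** Two tests per trainee, 90 days apart; one enrolment per person; cohorts every 3 months from 28 September 2019 to 28 November 2023 (50 months, 50/3 = about 17 cohorts); a 20-item test, so one item is 5 percentage points; 433 medical trainees; two-sided 0.05.

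**2. The plan's own figure.** With N=1500, z=1.96, p=q=0.5 and E=0.05: n = 1500 × 3.8416 × 0.25 / (0.0025 × 1499 + 0.9604) = 1440.6 / 4.7079 = 306.0, against 307 stated. Then 307 × 1.41 = 432.9, or 433. The figure reproduces to within one. It rests on a proportion approving the training, not on a score change.

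**3. What can be separated.** Write each score as a sum of five terms: intercept, calendar trend, course, within-trainee learning over 3 months, and retest.

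| Test | Course | Months since entry | Second sitting |
|---|---|---|---|
| Pre | 0 | 0 | 0 |
| Post | 1 | 3 | 1 |

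The last three columns are proportional for every trainee in every cohort. Over 17 cohorts the five-column design matrix has rank 3. Intercept and calendar trend are estimable; of the other three terms only the sum is. The course effect alone is not estimable. If untrained trainees tested at the same two times are added, the rank is 4 and the course effect becomes estimable (learning and retest stay joined to each other).

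**4. What autoregression does.** Modelling serial correlation changes standard errors and weights, not the proportionality in step 3. In 1,000 simulated series (17 cohort means before and after, SD 10, correlation 0.5, zero course effect, 3 points of natural learning), an AR(1) regression with a linear calendar trend and a course step gave a mean step of 2.98, significant in 99.9% of runs. None of the learning was removed. This model is more favourable than the plan, which describes ARIMA only as a test of autocorrelation and names no course term.

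**5. Size of the problem.** The article gives no SD, correlation or learning rate, so these are assumptions. For a paired comparison, SE of the mean gain = SD × √(2(1 − ρ)) / √n. With SD 15, ρ 0.5 and n 433: 15 × 1 / 20.81 = 0.72. With zero course effect and natural learning g, the chance of P<0.05 is Φ(g/SE − 1.96) + Φ(−g/SE − 1.96).

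- g = 1.5: 1.5/0.72 = 2.08, about 55%.
- g = 2.5 (half of one item): 2.5/0.72 = 3.47, about 93%.
- g = 2 at SD 10, 15, 20: SE 0.48, 0.72, 0.96, giving 99%, 79%, 55%.
- g = 2 with 307 trainees at SD 10, 15, 20: 94%, 65%, 42%.

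If the one-way ANOVA were run ignoring the pairing, the SE would be 15 × √(2/433) = 1.02, and the figures for g = 1.5 and 2.5 would fall to about 31% and 69%. The bias is the same size either way.

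**The case against.** **The protocol does not say the bias is solved.** The remedy is a hope, placed among the limitations, and attribution is deferred to a later randomized trial. The main objective is feasibility, and the null hypothesis is only that scores do not differ, which an uncontrolled comparison can answer. This stands: a reader might infer that the protocol declares the bias overcome, and that goes too far. What remains is that the remedy is the only answer offered to an admitted threat and cannot work, and that Statistical analysis still speaks of the effect of the training on scores.

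**Staggered cohorts do help.** Pre-tests of later cohorts are an untrained series over calendar time, so a calendar trend can be separated. This stands, but it does not touch learning by the same trainee over 90 days, or retest.

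**Is a better comparison already in the data?** A reader might infer that one mixed model, with a trained/untrained term adjusted for months of surgery rotation, would give the course effect. The documents do not support this. Every trained score is also a second sitting, and trainees rotate through several departments, so learning need not stop when surgery ends. In simulations with zero course effect, such a coefficient was about −0.1 when learning came only through rotation months. It was 2.9 with 3 points of general clinical learning, and 3.0 with a 3-point retest gain. Timing is also uncertain: an average of 12 sessions per site over 50 months is one every 4.2 months, so one cohort's post-test need not coincide with the next cohort's pre-test at that site.

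**Are the series too short?** A reader might add that 12 points per site make the ARIMA uninformative. The plan specifies models by trainee group, not by site, so a site-level limit cannot be pinned on it.

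**Conclusion.** The point holds in this form: the design and the ARIMA analysis as described cannot separate the course from three months of further clinical learning or from a second sitting, so the remedy offered in the limitations section is wrong. That conclusion follows from the measurement schedule and needs no numerical assumption. The size does: at SD 15, correlation 0.5 and 433 pairs, natural learning of 1.5 to 2.5 points produces a significant gain in about 55% to 93% of trials with no course effect; over SDs of 10 to 20, 2 points does so in 99% to 55%. It does not follow that the feasibility objective fails, or that the pre/post comparison is useless. It measures change in score, and the conclusion should go no further.

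**What to change.** 1. Describe the design as repeated uncontrolled before-after cohorts wherever it is called an interrupted time series.
2. In Study strengths and limitations, withdraw the statement that the time series and autoregression models overcome the problem. Say instead that natural learning and retest cannot be separated from the course. Keep the reference to the later randomized trial.
3. Limit the conclusion from the pre/post comparison to change in score, and reword the sentence in Statistical analysis on the training's effect by cadre to match.
4. Optionally, as a sensitivity analysis only, compare trained post-tests with untrained pre-tests from the same period, adjusting for calendar time, cadre, site and rotation exposure. State that it still carries retest and other within-trainee learning, and do not report it as the causal effect.

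Items 1 to 3 cost only wording. Item 4 needs rotation start dates, whose availability the article does not establish, and spread in exposure at entry. Its interval is wider: in simulation the SE was about 1.3 to 1.5 points against 0.72 for the raw gain, rising to about 6.5 if all trainees entered within their first month.

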## Research registration unique identifying number

This protocol has been retrospectively registered with research registry UIN researchregistry9490 hyperlink https://www.researchregistry.com/browse-the-registry#home/

## Data accessibility statement

All the de-identified data sets arising from this study protocol will be made publicly available as online supplemental material through a permanent weblink to a repository that will be provided by peer reviewed journal. The data collection instruments are available through the corresponding author.

## Provenance and peer review

Provenance and peer review not commissioned, externally peer reviewed.

## Study updates

Actively recruiting, first participant recruited 28 September 2019, last participant anticipated by 28 November 2023.
